### Participant characteristics

#### Inclusion

Zuni elders will be eligible to participate if they are Zuni tribal members aged 65 years and older who demonstrate elevated fall risk according to 2 or more of the following outcomes: (1) Timed Up and Go ≥ 12 s; (2) 30 Second Chair Stand Test below age and sex norms; (3) Inability to complete the Four Stage Berg Balance Test; (4) Four or more positive responses on the *CDC Stay Independent: Check Your Risk for Falling*; or (5) history of 2 or more falls during past year or one injurious fall during past year.

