Changes in strength and balance (TUG, 30 Second Chair Stand, and Four Stage Balance test) are the primary outcome measures for this study. The CHRs will perform these assessments at baseline, 3, 6, and 12 months. Falls incidence is a secondary outcome and compared between the intervention and education groups. Fall incidence will be monitored prospectively monthly by falls calendars. We note that the high level of clinical surveillance of Zuni elders by the Zuni Senior Centre makes them an ideal population to record fall incidence and minimizes recall bias. Participants will be asked to maintain a monthly fall calendar throughout the investigation. A fall will be defined as an unexpected event where an individual unintentionally comes to the ground or lower level [37]. The CHRs will ask participants if they have fallen at every home visit. If a fall is reported, details of the fall(s), timing of fall, information about injury, and other pertinent information will be attained through standardized questionnaire. If an acute injurious fall is reported, CHRs will utilize a protocol (to be developed) for referral to IHS for follow up care and evaluation for ongoing participation in the trial. The fall diary will allow for the determination of number of falls, number of injurious falls and fall rate per person year. Fall diaries are the gold standard in fall assessment [38]. Collecting information on timing of fall will also allow for the examination of impact of the intervention on fall incidence.

The analysis plan for Aim 3, the randomized controlled trial, will employ an intention-to-treat analysis. We will first compare baseline demographic and clinical characteristics, such as age, sex, and fall risk score, between study groups using chi-square tests for categorical data and t-tests for continuous data. This will enable us to evaluate the degree to which the randomization scheme balanced these characteristics between the study groups, stratified by falls risk. As we expect randomization to provide for equivalent study groups at baseline, we do not expect to need to adjust for baseline characteristics in our primary analyses. However, we will change these plans should there be major differences in participant characteristics between treatment arms.

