Falls incidence is not the primary outcome measure for this trial. Changes in balance and strength, as measured by the TUG, 30 Second Chair Stand, and Four Stage Balance tests will serve as primary outcome measures, which are important correlates of falls risk. We will employ linear mixed effects models to evaluate the significance of the treatment effect by testing for an interaction between treatment arm and time for these longitudinally measured assessments of the outcome measures. These models enable the efficient use of all measured data values while appropriately accounting for repeated measurements, and also the clustering that will be induced by stratified randomization of participants within household family units into strata defined by falls risk. Falls incidence is a secondary outcome. We will estimate and compare the incidence of falls observed within the two study groups over the study’s observation time using a score test from a Cox regression model that accounts for the clusters of individuals within household family units who were assigned to treatment groups within falls risk strata. In the absence of clustering, this is equivalent to a log rank test for time-to-event outcomes. This approach utilizes data from study participants, nested within household family units, while accounting for their time on study: those enrolled earlier in the study will have greater time in follow-up. We will also use Cox proportional hazards models to perform regression analyses that compare treatment groups while adjusting for potential differences in baseline characteristics.

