In summary, first, we will follow the intent-to-treat principle in our primary analyses. Second, we will additionally adjust for the potential bias created by contamination using a contamination adjusted intention-to-treat analysis through the use of an instrumental variables (IVs) approach [39]. Third, we will carefully evaluate modelling assumptions (e.g. normality and variance structures in the mixed models, and proportionality of hazards in the survival models) in order to extract appropriate conclusions from the data. We will take corrective action when necessary, such as applying data transformations, to ensure that statistical modelling assumptions are met by the data. Finally, we will evaluate the degree to which missing data might have on study conclusions by performing sensitivity analyses that implement different rules from those induced by the intent-to-treat principle. Should these analyses suggest that the results differ by data missingness, we will explore the use of multiple imputation approaches and pattern mixture modelling approaches to determine the degree to which results differ under various missing data assumptions before making a final conclusion from the between-group comparisons.

In addition to these primary analyses, we will conduct a series of additional analyses to determine the degree to which the comparisons of interest might be influenced by patient characteristics. In particular, we are interested in whether the study comparisons are confounded, or modified by falls risk or complications of diabetes such as orthostatic hypertension/dizziness. We will perform analyses that examine the degree of confounding of the intervention effects by including them as covariates in the primary analysis models, and examine the degree to which they might modify intervention effects by adding their interactions with treatment arm to the primary analysis models.

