#### Power and sample size

The primary outcomes of this study are changes in the TUG, 30 Second Chair Stand, and Four Stage Balance tests. These outcomes were selected because they are related to falls risk. Although the aim is to eventually demonstrate a reduction in falls incidence, the Zuni elder population is not big enough to provide adequate statistical power for this outcome. We do plan to extend the follow-up falls calendars to capture these outcomes, and this will provide critical information for future studies. The accepted degree of reduction in falls that is imparted by a traditional OEP is 32% [38, 39]. Because the percent reduction in falls does not directly correlate with a quantitative effect size that will be estimable from the data addressing our primary hypotheses, and because the outcome measures do not perfectly predict the probability of falls, it is likely that the detectable effect size that would be meaningful in the context of reducing falls would need to be a large one in order to suggest that the intervention is likely to have the desired effect on falls incidence. Therefore, the study was powered to detect at least moderate effect sizes. Specifically, we computed the number of participants to enrol into the study that would provide us with at least 80% power to detect an effect size of 0.67 for an improvement in the outcome measures over time between the treatment arms using a two-sided, 0.05 level test of between-group differences over time. Power estimates were obtained from linear mixed effects models that assumed within-subject correlations of 0.3, and within-cluster correlations of 0.1, and also corrected for 3 primary tests of significance. This computation suggested that data from 84 participants in each treatment arm would be required. In order to allow for the potential for dropouts, or for the possibility that the treatment might not be quite as efficacious as desired, 100 study participants per treatment arm will be enrolled. Even if 20% of the participants drop out of the study, this sample size will provide at least 80% power to detect effect sizes of 0.59 – nearly the target of 0.67, and still not a large effect size.

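### The main falls comparison leaves out past-year falls history, which screening already ascertains, and so gives up a modest amount of power on an outcome the protocol calls under-powered

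*Protocol article*

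**What the plan says.** All references are to the protocol article.

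- **Main falls test.** Data analysis plans (Aim 3) makes falls incidence a secondary outcome, compared "using a score test from a Cox regression model" that allows for clustering by household, with households assigned within falls-risk strata. It adds: "In the absence of clustering, this is equivalent to a log rank test for time-to-event outcomes".
- **Default on covariates.** The same section states that "we do not expect to need to adjust for baseline characteristics in our primary analyses", and that this will change if the arms turn out to differ in a major way.
- **Adjusted falls models.** Cox regressions will also be run, "adjusting for potential differences in baseline characteristics". No covariate is named.
- **Additional analyses.** Falls risk and diabetes complications will be examined as confounders "by including them as covariates in the primary analysis models", and as effect modifiers.
- **Falls history.** Inclusion criterion 5 is "history of 2 or more falls during past year or one injurious fall during past year". An elder needs any two or more of five criteria. Table 1 schedules a medical history and falls-risk screening at baseline.
- **Strata.** Randomization uses three levels of fall risk, not defined in the article, and takes the risk of the first family member enrolled.
- **Power.** Power and sample size concedes that "the Zuni elder population is not big enough to provide adequate statistical power for this outcome".

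**The concern.** The plan treats imbalance as the reason to adjust. In a linear model with balanced arms, adjustment mainly buys precision. In a Cox model there is a further effect. If a predictor of the event is left out, the hazard ratio moves toward 1 relative to the ratio at a fixed level of that predictor, and the test loses power, even when the arms are perfectly balanced.

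Falls history is a natural candidate predictor and is ascertained before randomization. Because any two of five criteria suffice, elders with and without recent falls can both enter each arm. The protocol says it cannot enlarge the population to power falls, so efficiency in the analysis is one of the few levers left. It also looks to the falls data to inform future studies. In addition, letting observed differences decide the adjusted model leaves the choice of covariates until after the data are seen.

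**Working it through.** **The plan's own figure.** The article gives no power or event count for falls, only the statement that power is inadequate. The 84 per arm applies to the strength and balance outcomes.

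**Inputs from the article**
- 100 per arm, 1:1 allocation, 20% dropout, 12 months of follow-up.
- A 32% reduction in falls, read here as a hazard ratio of 0.68 (Power and sample size).
- 32% of elders with at least one fall in three months (Background).

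**Assumptions not in the article**
- Constant hazard. This gives 12-month control incidence 1 − (1 − 0.32)^4 = 0.786, or a rate of −4 ln 0.68 = 1.54 per year. An incidence of 50% is also tried.
- Two-sided 0.05 for falls (stated only for the primary outcomes).
- 50% or 70% of elders with past falls, and past falls multiplying the hazard by 1.5, 2 or 3.

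**Step 1: is falls under-powered?** The Schoenfeld formula gives events needed = 4(1.960 + 0.842)² / (ln 0.68)² = 31.4 / 0.1487, which rounds up to 212. Events expected with 100 per arm and no dropout:
- Control 78.6%: the OEP arm has 1 − exp(−1.543 × 0.68) = 0.650. Events are 100 × (0.786 + 0.650) = 144, and power is 64%.
- Control 50%: the OEP arm has 0.376. Events are 88, and power is 44%.

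This agrees with the protocol's concession.

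**Step 2: what does adjustment add?** The simulation used 200 elders, 2,000 trials per scenario, a conditional hazard ratio of 0.68 and 20% uniform dropout. It compared the unadjusted score test with a Cox model adjusted for a binary past-falls variable. Households and falls-risk strata were not simulated.

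| Control incidence | Past-falls prevalence | Past-falls HR | Unadjusted HR, power | Adjusted HR, power | Gain (points) |
|---|---|---|---|---|---|
| 78.6% | 50% | 1.5 | 0.688, 57.8% | 0.682, 59.4% | 1.6 |
| 78.6% | 70% | 1.5 | 0.682, 59.1% | 0.676, 60.6% | 1.5 |
| 78.6% | 50% | 2 | 0.700, 52.8% | 0.685, 58.0% | 5.2 |
| 78.6% | 70% | 2 | 0.690, 56.0% | 0.677, 60.4% | 4.4 |
| 78.6% | 50% | 3 | 0.721, 47.8% | 0.681, 59.7% | 11.9 |
| 78.6% | 70% | 3 | 0.710, 50.4% | 0.682, 59.5% | 9.1 |
| 50% | 50% | 1.5 | 0.675, 41.2% | 0.671, 41.1% | −0.1 |
| 50% | 70% | 1.5 | 0.678, 40.6% | 0.676, 40.7% | 0.1 |
| 50% | 50% | 2 | 0.683, 40.1% | 0.677, 39.7% | −0.4 |
| 50% | 70% | 2 | 0.678, 40.3% | 0.672, 41.5% | 1.2 |
| 50% | 50% | 3 | 0.692, 38.2% | 0.671, 42.7% | 4.5 |
| 50% | 70% | 3 | 0.692, 37.2% | 0.681, 40.1% | 2.9 |

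Each power figure has a simulation standard error of about √(0.25/2000) = 1.1 points. Both tests were run on the same trials, so the gains are more precise than that. The small negative gains are noise around zero.

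**Step 3: sensitivity.** A second set of runs (1,500 trials per scenario, 80 or 100 per arm, a full year for all, control rate 1.54, half with past falls) gave gains of 5.1 to 12.5 points for past-falls hazard ratios of 2 to 3. Adding unexplained variation between persons (gamma frailty, variance 0.5) cut these to 2.5 to 5.9 points.

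**Step 4: size of the shift.** The largest shift is from 0.681 to 0.721, which is 0.04. On the log scale it is ln(0.721/0.681) = 0.057. With 135 events the standard error is about 2/√135 = 0.172, so the shift is about a third of one standard error.

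**The case against.** The strongest reply is that this is an efficiency preference on a secondary outcome, of a kind often left to an analysis plan that is not shown here. A log-rank-type test is valid in a randomized trial. The article also promises adjusted Cox models, promises further models with falls risk as a covariate, stratifies the randomization by fall risk, and describes the test in terms of those strata.

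Much of this stands:
- It would be wrong to infer that no falls analysis is adjusted. Adjusted models are planned.
- It would be wrong to infer that the score test is biased. The shift is non-collapsibility, and the unadjusted ratio is a valid marginal effect.
- If the strata reflect falls history and the test is stratified on them, part of the gain is already taken. The simulation does not credit this.
- Eligibility may weaken the contrast. An elder who meets criterion 5 needs only one other criterion, while an elder who does not needs two others.
- Criterion 5 is a yes/no composite. That every elder's falls are recorded as a count is an inference from Inclusion and Table 1.

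The reply does not remove the point. The article states a choice and its reason rather than staying silent: no adjustment unless imbalance appears. The promised models are additional, aimed at imbalance or confounding, and do not name falls history. The strata are undefined in the article, and later members of a household carry the first member's level. The log-rank remark leaves it unclear whether the test is stratified at all.

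**Conclusion.** The point holds as a modest, nearly free gain and not as an error in the test. Adjusting for past-year falls history would add about 0 to 12 power points across control incidences of 50% to 79%. The past-falls hazard ratio and prevalence are assumptions, so the upper end should not be read as the expected gain. The increment over the test as planned is smaller to the extent that the strata already carry falls history.

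A reader might infer that adjustment would rescue the falls comparison. It would not: adjusted power ran from about 40% to 61% in Step 2 and stayed below 80% in every scenario, so the protocol's conclusion about power is unchanged.

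**What to change.** In Data analysis plans (Aim 3, falls incidence), name past-year falls history as a covariate in the main falls Cox model, fixed in advance and kept whatever the baseline balance. Use a count such as 0, 1, 2 or more if it is recorded for every elder, and otherwise criterion 5 as yes/no. Keep the falls-risk strata, use a household-robust variance, and report the unadjusted score test as supporting.

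The cost is a change of wording and one or two degrees of freedom. The main hazard ratio then becomes covariate-specific rather than marginal, and the report should say so.

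### Multiple imputation and pattern-mixture analyses wait on a first check that, depending on its unnamed rules, may not reveal informative dropout

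*Protocol article*

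**What the plan says.** All of this is in the Data analysis plans section of the protocol article.

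- **Primary principle:** "we will follow the intent-to-treat principle in our primary analyses".
- **Primary model:** linear mixed effects models for the Timed Up and Go, the 30-second chair stand and the four-stage balance test, tested through the arm-by-time interaction. On incomplete data the article says: "These models enable the efficient use of all measured data values while appropriately accounting for repeated measurements".
- **First look at missing data:** "sensitivity analyses that implement different rules from those induced by the intent-to-treat principle". The rules are not named.
- **Second look:** "Should these analyses suggest that the results differ by data missingness", then "we will explore the use of multiple imputation approaches and pattern mixture modelling approaches". This step is meant to show how far results change under different missing-data assumptions before a final conclusion is drawn.

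For Aim 4 the article promises sensitivity analyses for drop-out and missing data, with no condition and no named method. Nowhere does it state an unconditional analysis of the three primary outcomes under a missing-not-at-random assumption.

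**The concern.** A mixed model fitted to all measured values handles missing outcomes correctly only if they are missing at random. Whether they are cannot be learned from the observed data. An analysis of completers, or of a per-protocol set, uses a different selection of the same observed values and says nothing new about the unseen ones. The two can agree while both are wrong. If that agreement closes the question, the pattern-mixture models, which do vary the assumption, stay unused in the situation they exist for.

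The article makes informative dropout plausible, though it does not show that it will occur. It plans for up to 20% attrition in elders selected for raised fall risk. It has participants with an acute injurious fall evaluated for continued participation. It also describes continued home exercise as the key to keeping the benefit. At stake is the robustness claim attached to the primary result, not the primary test itself.

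**Working it through.** The plan gives no figure for this point, so there is nothing to reproduce. The check is one of logic, with two illustrative simulations.

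**Inputs from the Power and sample size section:** "100 study participants per treatment arm will be enrolled"; "Even if 20% of the participants drop out of the study"; within-subject correlation 0.3; target effect 0.67 SD. **Assumed here:** the dropout mechanisms, and a completers analysis as one possible form of the unnamed rules.

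**1. Size of the error by formula.** Let p be the proportion leaving in each arm, d_s the effect in stayers and d_l the effect in those who leave the exercise arm.

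- All-randomised effect = (1 − p) × d_s + p × d_l.
- If leavers are unseen and cannot be told apart by their earlier values, both completers and a missing-at-random analysis estimate d_s.
- Overstatement = p × (d_s − d_l).

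With p = 0.20 and d_s = 0.67:

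| Assumed effect in leavers | All-randomised effect | Overstatement |
|---|---|---|
| 0.67 (all kept) | 0.670 | 0 |
| 0.335 (half kept) | 0.536 + 0.067 = 0.603 | 0.067 |
| 0 (none kept) | 0.8 × 0.67 = 0.536 | 0.134 |

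**2. Simulation of the last row.** 100 per arm, dropout after month 3, outcome at month 6. Over 400 trials the completers estimate averaged 0.667 and the missing-at-random estimate 0.673. Over 4,000 trials they averaged 0.670 and 0.669, with a true all-randomised effect of 0.534. The mean gap between the two analyses was 0.000 (SD across trials 0.047), so the comparison carried no systematic signal.

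**3. Simulation with a true effect of zero.** 100 per arm, four visits, 20% missing at 12 months, 4,000 trials, household clustering ignored. Dropout was random in the control arm. In the exercise arm it followed the mechanism shown, except in the first row, where it was random in both arms.

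| Dropout in exercise arm | Missing-at-random estimate | Completers | Gap (SD) |
|---|---|---|---|
| Random | 0.003 | 0.003 | 0.000 (0.055) |
| Depends on the 12-month value | 0.275 | 0.220 | −0.055 (0.056) |
| Depends on the part of the 12-month value not predicted by earlier visits | 0.279 | 0.278 | −0.001 (0.055) |

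In the third row both analyses are wrong by about 0.28 SD and their gap looks the same as under random dropout. In the second row the gap shifts by about one SD of its chance variation. The plan states no threshold. If one took twice the chance SD, 2 × 0.055 = 0.11, the normal approximation gives (−0.11 + 0.055) / 0.056 = −0.98, so the check would fire in roughly 16% of trials.

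**4. A different kind of first-step rule.** Suppose the rule is baseline carried forward, so that change is 0 for the 20% leaving in each arm. With c the control-arm change, the estimate is 0.8 × (c + 0.67) − 0.8 × c = 0.536. That differs visibly from 0.67, so the check would fire. It gives the same 0.536 when leavers keep their full benefit, so the gap arises from the rule and does not diagnose informative dropout.

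**The case against.** The strongest reply is that the first-step rules are unnamed. The sentence could cover rules that fill in missing values, such as baseline carried forward or worst case, and the working shows that one of these would open a gap in the same scenario. That stands: the weakness is established for rules that merely reselect observed data and not for every rule the sentence allows. A fill-in rule would get the second step run, but for a reason unrelated to whether dropout is informative.

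Second, a reader might infer that the check can never detect informative dropout. That is too strong. When dropout depended on the 12-month value, the completers result did move, by 0.055 SD. The supportable statement is that the check cannot detect it reliably, and that a quiet first step is no reassurance. The mechanism giving exact agreement was constructed to show this.

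Third, the wording is tentative, it does not forbid running the later methods anyway, and a journal article leaves thresholds and exact methods to the analysis plan. The missing threshold and missing detail are therefore not held against it. What remains is the sequence the article does state: the methods that vary the missing-data assumption follow if an earlier check raises an alarm. An analysis plan written faithfully from it would inherit that order. The unconditional promise for Aim 4 names no method, and the article does not state one for the primary outcomes.

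**Conclusion.** The point holds in a limited form. The plan makes its missing-not-at-random work depend on a first check that, if it only changes who or which observed values are analysed, cannot reliably rule out informative dropout.

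No size of bias can be stated for this trial. The contrast of about 0.67 with 0.54 shrinks to nothing as the assumed effect in leavers rises to that in stayers.

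Two stronger readings are not supported:

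- A reader might infer that the trial will overstate its effect by about 25%. That figure is simply 1 / 0.8 = 1.25, the direct result of assigning zero benefit to leavers. The documents give no evidence for that loss, and the 20% is only a sample-size allowance.
- A reader might infer that the trial abandons intention to treat. It does not: the primary analyses keep it, and sensitivity analyses outside it are ordinary and not an error in themselves. The fault lies only in using them as the gate.

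The primary test and the sample size are unaffected.

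**What to change.** Remove the condition. State that, for each of the three primary outcomes, a prespecified pattern-mixture sensitivity analysis will always be reported beside the primary result, with all randomised participants kept in their assigned arm. Delta-adjusted multiple imputation over a stated range is one suitable form. Reference-based imputation is another reasonable choice, and the exact form can be left to the trial statistician, provided it is fixed before outcome data by arm are seen. Keep analyses outside intention to treat as supplementary, name their rules, and do not let them decide whether the missing-data analyses are run.

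The cost is a little extra analysis work with method families the article already names. No data collection, sample size or primary test changes.

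### The effect-modification rule for the three primary outcomes adds modifier-by-arm, but the plan's treatment effect is arm-by-time, so the term estimates a diluted quantity rather than modification of that effect

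*Protocol article*

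**What the plan says.** All of this is in the protocol article.

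- **Outcomes (Power and sample size).** "The primary outcomes of this study are changes in the TUG, 30 Second Chair Stand, and Four Stage Balance tests".
- **Visits (Data analysis plans).** "The CHRs will perform these assessments at baseline, 3, 6, and 12 months".
- **Treatment effect (Data analysis plans).** Linear mixed models will "evaluate the significance of the treatment effect by testing for an interaction between treatment arm and time". On the data used: "These models enable the efficient use of all measured data values while appropriately accounting for repeated measurements".
- **Power basis (Power and sample size).** The target is "at least 80% power to detect an effect size of 0.67 for an improvement in the outcome measures over time between the treatment arms". The significance level is 5%, two-sided.
- **Effect modification (Data analysis plans, additional analyses).** The trial asks whether the comparisons are confounded or "modified by falls risk or complications of diabetes such as orthostatic hypertension/dizziness". To answer the second part it will "examine the degree to which they might modify intervention effects by adding their interactions with treatment arm to the primary analysis models".

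The last rule does not separate the mixed models for the primary outcomes from the Cox models for falls. No modifier-by-arm-by-time term appears anywhere in the article.

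**The concern.** In a model where the treatment effect is arm-by-time, a modifier changes that effect only through a term that contains time. A modifier-by-arm term has the same value at every visit. It shifts the arm contrast by one constant, at baseline as much as at month 12, and leaves the arm difference in change identical at all levels of the modifier. The stated question is whether the intervention effect differs by falls risk or diabetes complications. The stated term answers another one: whether the arm difference, averaged over visits that include a pre-treatment visit, differs by modifier.

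What is at stake is the interpretation of an analysis in which the trial declares a particular interest, on a characteristic that is also the randomization stratifier. A diluted coefficient could be reported as the difference in intervention effect and read as a near-uniform benefit across risk levels.

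**Working it through.** **1. What the written model implies.** Let M be the modifier. With arm, time, arm x time, M and M x arm in the model, the arm contrast at visit t and level M is a + b_t + g x M. The arm contrast in change from baseline is (a + b_t + g x M) - (a + b_0 + g x M) = b_t - b_0. M cancels, so the model holds the plan's treatment effect constant over M. Adding modifier x time does not alter this.

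**2. What g estimates.** With complete data and compound symmetry, g is the modifier difference in the arm contrast, averaged equally over the four visits. Write the true modification at 0, 3, 6 and 12 months as a fraction of its full size. It is zero at baseline, because no treatment has been given.

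- Full from month 3: (0 + 1 + 1 + 1)/4 = 0.75
- Reached at month 6 and held: (0 + 0.5 + 1 + 1)/4 = 0.625
- Linear to month 12: (0 + 0.25 + 0.5 + 1)/4 = 0.4375
- Peak at month 6, half lost by month 12: (0 + 0.5 + 1 + 0.5)/4 = 0.50

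For a modification of 0.67 SD these give 0.50, 0.42, 0.29 and 0.34. The fractions do not depend on the correlation, the sample size or household clustering.

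**3. Power.** The plan states no figure for this analysis, so there is none to reproduce. Inputs from the article: 84 per arm, visits at 0, 3, 6 and 12 months, within-subject correlation r = 0.3, two-sided 0.05. Assumptions: a binary modifier split 50:50 (42 per cell), compound symmetry, SD 1, no household term, a modification of 0.67 (the plan's main-effect target, borrowed for scale), and r = 0.5 and 0.7 as alternatives.

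The standard error is sqrt(4v/42), where v is the variance of the within-person contrast:

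- Two-way (mean of four visits): v = (1 + 3r)/4
- Three-way slope, time scaled 0, 0.25, 0.5, 1: v = (1 - r)/0.546875
- Three-way follow-up mean minus baseline: v = (1 - r) x 4/3

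At r = 0.3 the standard errors are 0.213, 0.349 and 0.298. Power is Phi(estimate/SE - 1.96) plus a negligible opposite tail. Example, linear profile: 0.293/0.213 = 1.38, power 28%; slope 0.67/0.349 = 1.92, power 48%. The last column is the three-way test with categorical time (3 df, noncentral chi-square).

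| Profile | r | Two-way | Slope | Follow-up minus baseline | 3 df |
|---|---|---|---|---|---|
| Linear to 12 | 0.3 | 28% | 48% | 26% | 33% |
| | 0.5 | 22% | 62% | 34% | 45% |
| | 0.7 | 19% | 83% | 52% | 69% |
| Held from 6 | 0.3 | 50% | 46% | 47% | 41% |
| | 0.5 | 40% | 60% | 60% | 55% |
| | 0.7 | 34% | 81% | 82% | 80% |
| Full from 3 | 0.3 | 66% | 34% | 61% | 44% |
| | 0.5 | 54% | 44% | 76% | 59% |
| | 0.7 | 46% | 65% | 93% | 83% |
| Peak at 6 | 0.3 | 35% | 14% | 32% | 31% |
| | 0.5 | 28% | 18% | 43% | 42% |
| | 0.7 | 23% | 27% | 63% | 65% |

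At r = 0.3 the two-way test matches or beats every three-way version except under linear growth, where the slope and 3-df tests beat it. At 0.5 the three-way test is ahead except for the slope contrast under an early or a peaking effect. At 0.7 it is ahead throughout.

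**4. Type I error.** Randomization makes the expected baseline arm difference zero at each modifier level. With no modification the two-way coefficient therefore has expectation zero and the test keeps its 5% level.

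**The case against.** **Shorthand.** The sentence covers two kinds of model at once, names the right target, and may mean interactions with whatever term carries the treatment effect. An article need not list every term of an exploratory model. That reading is possible, but nothing in the text says so. The sentence names both the term and the model it enters, and an analyst who follows it fits the wrong term. For the Cox models the rule is right as it stands.

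**Baseline may not be a response.** The outcomes are called changes. If change from baseline at 3, 6 and 12 months is the response, modifier x arm contains no baseline visit and the dilution disappears. This stands as a condition on the point. The use of all measured values favours baseline as a response. So does the arm-by-time test itself: with change scores as the response, an effect present in full by month 3 and held would produce no arm-by-time interaction.

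**Power.** A reader might infer that real modification would often be missed because of this term. The documents do not support that. At the only within-subject correlation the plan states, the two-way test is often as good or better, and the article does not fix the time contrast on which a three-way test would be judged. The slope contrast can itself be attenuated: 0.31 of 0.67 under the peak-at-6 profile, slightly worse than the two-way 0.34.

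**Spurious modification.** A reader might also infer that baseline imbalance within a stratum would create false modification. Under randomization, stratified by falls risk, such imbalance is chance. It adds noise to the estimate but does not raise the error rate.

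**Conclusion.** The point holds as a mismatch between the effect the plan defines and the term it uses to test modification of that effect. For the three primary outcomes, the modifier-by-arm coefficient is not a difference in intervention effects on change. It recovers 75% of a modification constant from month 3 and about 44% of one growing linearly to month 12.

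This rests on baseline being one of the repeated responses and, for the exact fractions, on complete data. The power figures rest further on the binary 50:50 modifier, compound symmetry, no household term and the assumed profiles; only the 0.3 correlation is the plan's own. Power is therefore not the main argument, and its direction varies.

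The analysis is additional. The primary tests, the sample size and the error rate are untouched. The consequence is a misdirected and attenuated estimate in an analysis the trial singles out, and it is worth correcting before the data are analysed.

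**What to change.** In the additional-analyses paragraph of Data analysis plans, separate the two model types:

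- **Mixed models for TUG, chair stand and Four Stage Balance:** test modification by modifier x arm x time with all lower-order terms, including modifier x time, on the same time contrast as the primary analysis. If change from baseline is the response, say so; modifier x arm is then the term to use.
- **Reporting:** give the arm effect on change, with its interval, within each level of the modifier.
- **Cox models for falls:** keep modifier x arm.

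The cost is a sentence and a few model terms, with no new data or participants. The downside is lower power in some low-correlation scenarios with an early or held effect (for example, 61% instead of 66% for an effect present in full from month 3 at correlation 0.3, or 34% if the primary contrast is a linear slope).
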